# Efficacy of blended digital and face-to-face psychotherapy compared to enhanced psychotherapy for patients with Somatic Symptom Disorder (iSOMA+): study protocol for a multicenter randomized controlled pragmatic trial

**DOI:** 10.1186/s13063-026-09886-y

**Published:** 2026-07-10

**Keywords:** Persistent somatic symptoms, Somatic Symptom Disorder, Blended psychotherapy, Internet intervention, Randomized controlled trial

## Abstract

**Background:**

Persistent somatic symptoms (PSS) that occur in various somatic, functional, or mental health conditions can lead to considerable psychological distress and functional impairment. As such, they are a key characteristic of the Somatic Symptom Disorder (SSD) in DSM-5. While psychological treatments such as cognitive behavioral approaches can address these symptoms, their clinical efficacy in reducing symptom burden in previous trials remains limited. Blended psychotherapy, i.e., combining face-to-face psychotherapy with digital elements, is a promising new approach to efficiently enhance psychotherapeutic effects. This study therefore aims to evaluate the efficacy, mechanisms, and safety of blended psychotherapy compared to enhanced standard psychotherapy for individuals with SSD in outpatient psychotherapy.

**Methods:**

A two-armed, multicenter randomized controlled pragmatic trial will be conducted, and *N* = 250 adults with SSD will be randomized to either blended psychotherapy (20 individual sessions of cognitive behavioral therapy (CBT) + accompanying digital intervention; iSOMA+) or enhanced CBT (20 sessions of CBT + self-help booklet; CBT+). Participants are recruited at eight German university outpatient psychotherapy clinics. Assessments will be conducted at patient study inclusion (pre-treatment), during treatment, post-treatment, and 6 months follow-up. The primary outcome is the reduction in somatic symptom severity using the Screening for Somatoform Disorders (SOMS-7R) from baseline to post-treatment. Secondary outcomes include changes in symptom-related distress, coping, self-efficacy, as well as depression, anxiety, health anxiety, disability, quality of life, interpersonal relationship experiences and patient safety. Additionally, several potential moderators and mediators, including patient and intervention characteristics, will be examined.

**Discussion:**

This trial investigates the potential of blended CBT for improving treatment outcomes in patients with SSD and will provide evidence on the effects of active vs. passive self-help as treatment augmentation under pragmatic care conditions. By identifying prescriptive factors of treatment response, the study will support personalized care and contribute to more accessible and efficacious treatment options for patients with PSS.

**Trial registration:**

German Clinical Trials Register (DRKS) DRKS00035250. Registered on 13.06.2025, https://drks.de/search/de/trial/DRKS00035250.

## Administrative information

Note: the numbers in curly brackets in this protocol refer to SPIRIT checklist item numbers. The order of the items has been modified to group similar items (see http://www.equator-network.org/reporting-guidelines/spirit-2013-statement-defining-standard-protocol-items-for-clinical-trials/).

**Table Taba:** 

Title {1}	Efficacy of blended digital and face-to-face psychotherapy compared to enhanced psychotherapy for patients with Somatic Symptom Disorder (iSOMA+): Study protocol for a multicenter randomized controlled pragmatic trial
Trial registration {2a and 2b}	The trial is registered at the German clinical trials registry DRKS: DRKS00035250 (https://drks.de/search/de/trial/DRKS00035250). The trial was registered on 13.06.2025.
Protocol version {3}	2026-06-18. Version 2.0.
Funding {4}	This study is funded by the German Research Foundation (DFG, Clinical Studies, Project Number 543351897).

## Introduction

### Background and rationale {6a}

Persistent somatic symptoms (PSS), that occur on most days over several months, including but not limited to pain, fatigue, bowel dysfunctions, palpitations, or others, are widespread in the general population [1, 2], and even more prevalent in medical settings, where rates of up to 49% have been reported [3]. PSS may develop following medical conditions (e.g., infections, injuries) or procedures (e.g., surgeries), after stressful life events, or de novo, with the onset and even more their persistence assumed to result from an interplay of various biopsychosocial risk factors [4]. PSS can be associated with significant impairment [5] and psychological distress [6, 7], as mirrored in increased disability-adjusted life years and health care costs [8, 9]. PSS can be present in various somatic, functional, and psychological conditions and as such are a central feature of various disease classifications, including Somatic Symptom Disorder (SSD) in DSM-5. SSD is characterized one or more distressing and/or impairing somatic symptoms accompanied by excessive and dysfunctional cognitive (e.g., worrying), affective (e.g., health anxiety), or behavioral reactions (e.g., frequent medical care utlization). While prevalence rates are lower than for the much broader concept of PSS, SSD, and former, related diagnostic concepts can be considered one of the most common and burdensome mental disorders in most western countries [10], affecting 5–7% of the general population [11] and up to 78% in clinical populations [6]. Comorbidity with other mental disorders is common [11–13], and suicidality is frequently associated [14, 15]. Treatment guidelines recommend a primary care-centered biopsychosocial approach that includes addressing the underlying pathophysiology, person-centered communication techniques, and symptomatic pharmacological relief [16]. In more complex cases, for example, with debilitating somatic symptoms and/or severe psychological comorbidity, targeted psychological and pharmacological interventions are indicated [17, 18]. Among these, the best evidence exists for cognitive behavioral therapy (CBT) in reducing symptom severity, distress, and functional impairment [19].

However, the efficacy of psychotherapeutic treatment options remains suboptimal, with only small to moderate effects compared to control groups according to meta-analyses of previous RCTs [18, 20]. Moreover, access to adequate care remains challenging [21], with patients often perceived as “difficult to treat” and many affected individuals remain psychologically untreated [21, 22]. To address these challenges, innovative treatment approaches are required. Blended psychotherapy, which combines face-to-face therapy with digital therapeutic elements, represents a promising new approach that might enhance the efficacy (i.e., boosting treatment effects) or efficiency (i.e., reallocating therapeutic resources) of psychotherapy [23]. Blended interventions may be used sequentially (e.g., stepped-care models in pre- or post-treatment phase) or integrated into ongoing therapy [23, 24]. Compared to stand-alone digital programs, which have proven to be effective but limited in uptake and acceptance [25–28], blended formats offer greater therapeutic range and higher acceptance by both patients and therapists [26, 29–31]. While blended psychotherapy is a rather new field in mental health care, one of the first systematic reviews, particularly focusing on depression, anxiety, and substance use disorders, provides evidence for its effectiveness, showing reduced drop-out rates and decreased therapist time requirements [23]. Integrated blended psychotherapy shows positive effects for depression, but mixed or non-significant results for anxiety disorders [32]. Furthermore, meta-analytic findings support the augmentation of treatment effects of face-to-face therapy through the additional use of mobile technologies across various disorders, compared to standard treatment [33]. For example, Berger et al. [34] found that a combination of outpatient psychotherapy with an additional unguided online intervention was more effective than face-to-face therapy alone in patients with depression, yielding a medium-sized effect. In the context of chronic somatic conditions, previous combined care approaches have primarily focused on supplementing primary medical care with brief digital self-management programs, yielding mixed evidence regarding their effectiveness [35, 36]. To date, no systematic evaluation of blended psychotherapy for PSS or SSD exists. Given the limited efficacy of previous short-term psychological interventions [37] and the positive dose-response relation for treatment success [38], an integrated blended psychotherapy may offer a resource-efficient and scalable path to improving outcomes in secondary (specialized) care for SSD beyond the primary care level.

### Objectives {7}

The primary objective of this trial is to investigate the efficacy, that is to show that an integrated form of blended psychotherapy (iSOMA+) reduces somatic symptom severity significantly stronger than CBT enhanced with bibliotherapy (CBT+) from baseline to post-treatment.

Furthermore, we expect that iSOMA+, compared to CBT+, will lead to significantly greater reductions in secondary outcomes, including somatic symptom severity, adverse consequences of somatic symptoms, depression, anxiety, health anxiety and disability as well as significantly greater improvements in self-efficacy, somatic symptom coping, quality of life and experience in personal social systems from baseline to post-treatment and from baseline to the 6-month follow-up.

Thirdly, we expect that iSOMA+, compared to CBT+, will lead to a significantly higher rate of meaningful clinical change (response, remission) in somatic symptom severity.

Fourthly, we will investigate mechanisms of action, since previous trials have identified that motivational (e.g., self-efficacy, treatment agency) and functional (e.g., pain-related disability) characteristics are positively associated with treatment outcomes and may act as mediators of therapeutic change [39–41]. However, their role in blended psychotherapy is unclear. Therefore, we test whether an increase in self-efficacy, treatment agency, and a reduction in functional impairment will mediate the treatment effect of iSOMA+ compared with CBT+.

Exploratively, we will investigate to what extent (a) demographic characteristics of patients (e.g., gender), (b) clinical characteristics (e.g., baseline severity of somatic symptom distress, comorbidity), and (c) treatment-related factors (e.g., concurrent treatments, treatment expectations) moderate the treatment effect between the two treatment conditions (iSOMA+ vs. CBT+).

Furthermore, we will examine whether iSOMA+ differs from CBT+ with respect to changes in health care utilization from baseline to the end of treatment and from baseline to the 6-month follow-up. Treatment satisfaction and implementability will be tested. Finally, patient safety will be investigated, and no significant differences are expected in the type or frequency of serious adverse events (SAEs) and other side-effects between iSOMA+ and CBT+.

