### Trial design {8}

This is a prospective, multicenter, two-armed, active-controlled, parallel group, randomized controlled superiority trial that will be conducted at eight university outpatient psychotherapy centers in Germany. A total of 250 adult patients with SSD will be included, 125 patients per study arm. Participants will be randomly allocated to the two conditions. Both study groups receive 20 sessions of CBT. Additionally, the intervention group receives the iSOMA internet intervention, while the active control group receives a self-help booklet. Primary and secondary outcomes will be measured before randomization (baseline), during the course of treatment, after completion of the face-to-face treatment (post-assessment), and 6 months after end of treatment (follow-up) (see Fig. 1).

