*Secondary outcomes* will be assessed at baseline, post-treatment and at the 6-month follow-up and will include the following constructs and questionnaires: adverse psychobehavioral consequences of somatic symptoms (Somatic Symptom Disorder – B Criteria Scale, SSD-12 [73]), symptom coping (Pain Coping Questionnaire, FESV, coping subscales [75]), health related self-efficacy (Pain Self-Efficacy Questionnaire, FESS [79]), depression (Patient Health Questionnaire – depression scale, PHQ-9 [74]), anxiety (Generalized Anxiety Disorder, GAD-7 [76]), health anxiety (Whiteley Index, WI [77]), disability (Pain Disability Index, PDI [44]), quality of life (World Health Organization Quality of Life questionnaire, WHOQOL-BREF [78]), and experience in personal social systems (Experience in Personal Social Systems Questionnaire, EXIS.pers [64]). *Mediators* of treatment effects will include self-efficacy (assessed via FESS), treatment agency (assessed via the therapy-oriented processing subscale of the Therapeutic Agency Inventory, TAI [39, 65]), and disability (assessed via PDI). Mediators will be assessed at baseline, during treatment (sessions 1, 5, 10, 15), post-treatment, and at follow-up. *Potential moderators* of the treatment-related change processes will be explored. These will be assessed at baseline and will include (a) demographic variables, (b) clinical characteristics (e.g., comorbidity, baseline symptom severity, traumatic experience via the Childhood Trauma Screener (CTS [63])), and (c) treatment characteristics (e.g., parallel treatments, type of referral, preferences, treatment expectations assessed via the Generic rating scale for previous treatment experiences, treatment expectations, and treatment effects (GEEE [68])). Health care utilization (Health care Utilization Questionnaire, HCU [80]) will be assessed at baseline, post-treatment and at follow-up. In addition, therapist behavior and therapeutic alliance will be assessed during treatment (sessions 1, 5, 10, and 15) using the Warmth & Competence Scale (W&C [69]) and the Working-Alliance Inventory – short revised (WAI-SR [72]). General treatment satisfaction will be assessed post-treatment using the Client Satisfaction Questionnaire (ZUF-8 [81]), and module-specific satisfaction and perceived effectiveness of iSOMA will be assessed using self-constructed items. The extent to which iSOMA is a normal part of the daily working routine of therapists will be assessed post-treatment with the Normalization Measure Development questionnaire (NoMAD [67]). In both study conditions, adherence and duration of intervention use will be continuously monitored throughout the treatment period using self-constructed items. Self-rated negative treatment effects will be assessed post-treatment by the Negative Effects Questionnaire (NEQ [66]). Psychotherapists will provide sociodemographic data and indicate treatment preference at baseline and monitor SAEs and events of special interest (ESIs) and protocol deviations throughout treatment (sessions 1, 5, 10 and 15), post-treatment and at follow-up (administered by study personnel).

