
### Sample size {14}

Short-term CBT has demonstrated predominantly small to medium-sized between-group effects on somatic symptom severity in patients with medically unexplained physical symptoms or somatoform disorders (Standardized Mean Difference; *SMD* = 0.37; [18]) and medium- to large-sized within-group effects (*SMD* = 0.80; [83]), as corroborated by a multicenter CBT trial in outpatients with PSS (Cohen’s *d* = 0.70; [51]). Stand-alone internet-delivered CBT yielded small-sized average between-group effects on this outcome (*SMD* = 0.35; [84]) across chronic pain and functional somatic syndromes, whereas evidence from RCTs in individuals with diagnosed/probable SSD demonstrated medium- to large-sized effects (*d* = 0.68 to 0.91) [57, 85]. Evidence from depression research indicates small to medium-sized effects (*d* = 0.32 to 0.51) [34, 86] of added internet interventions to outpatient psychotherapy, which mirrors the treatment setting in the current study. Taken together, we expect the difference between our blended treatment and the enhanced treatment to be *d* = 0.40 for the primary endpoint. Thus, with a power of 80%, and a significance level of 0.05 (two-sided), 200 patients are required, when using a t-test. Because of some variability in effect sizes in the literature and the multicenter study introducing additional heterogeneity we planned the sample size conservatively by not using any correlation between measurements or between outcome and baseline variables. Based on treatment studies in this research field we expect a study drop-out for our primary endpoint (t1) up to 20% [51, 87], resulting in a sample size of *N* = 250 (125 per group). A study in the same setting concluded a similar sample size of 194 [51]. The calculation was performed with SAS 9.4.

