## Statistical methods

### Statistical methods for primary and secondary outcomes {20a}

The *primary endpoint* will be analyzed with a linear mixed-effect model (LMM) including center, use of prescribed psychopharmaceutic (ATC code N06A, yes/no), use of other (non-psychopharmaceutic) medications such as analgesics or antihypertensives (yes/no), mental disorder comorbidity (yes/no), intervention, time point, and the interaction term of intervention and time point as fixed effects, as well as baseline value as a covariate. An autoregressive covariance structure will be used as the primary covariance structure, given the ordered repeated measurements and the expected decrease in correlations over time. Robustness will be assessed using alternative covariance structures. The mixed-effects model uses all available observations and provides valid inference under the missing-at-random assumption. Model assumptions will be checked by residual plots and sensitivity to handling of missing data using multiple imputation. The test used is a linear contrast between the groups at post-treatment (time as categorical variable) and uses a *t*-statistic. Treatment differences will be displayed by adjusted mean differences and 95% confidence intervals. Follow-up data will be analyzed by the LMM approach taking a different contrast. The primary analysis will be performed with the ITT-population. For sensitivity additional subpopulations will be analyzed. Descriptive statistics will also be provided over time by treatment and in total. The primary parameter will also be displayed over time by a boxplot. For sensitivity also response and remission in the SOMS-7R are analyzed. Response will be operationalized as percentage improvement relative to the respective baseline score, (≥ 50% improvement within the pathological range of the SOMS-7R + 25% within the full range [93]). Remission will be coded if patients fulfill response criteria and transition from a dysfunctional to a functional score range in the SOMS-7R. As another remission criterion, we will analyze group differences in diagnostic status (SSD criteria fulfilled) at post-treatment and follow-up. Response and remission will be analyzed within a logistic regression model for each time point with the same covariates as the primary model. Descriptive statistics (absolute and relative frequencies) by time point will also be provided. Continuous secondary outcomes will be analyzed within an analysis model analogous to the primary analysis model and descriptive statistics will be given. Variables expected to have a skewed distribution like working disability days will be analyzed by Wilcoxon Rank Sum test. Categorical outcomes will be analyzed by Χ^2^-tests and will also be displayed by absolute and relative frequencies. Exploratively, health care utilization will be analyzed descriptively at the item level and compared between treatment groups. We will descriptively analyze the extent to which iSOMA is a normal part of the daily working routine of therapists’ post-treatment with the NoMAD. We will test group differences in the type and frequency of self-reported side effects in the NEQ with Χ^2^-tests and independent *t*-test for severity ratings. Potential moderators of the change processes between treatments include (a) demographics, (b) clinical characteristics (e.g., comorbidity, baseline symptom severity, traumatic experience via the CTS), as well as (c) treatment characteristics (e.g., parallel treatments, type of referral, preferences, treatment expectations via GEEE) at baseline. Mediators will be assessed at baseline, during treatment (sessions 1, 5, 10, 15), post-treatment, follow-up. We will examine the temporal, contemporaneous, and between-subject interaction of the therapists’ warmth and competence, treatment expectations, alliance, and psychotherapy outcomes with network models. To test the mechanisms of action of the blended therapy, mediating variables (self-efficacy, disability, and treatment agency) will be analyzed with structural equation modelling (SEM), assuming a lagged effect of a respective mediator on the primary outcome (dual simplex model [94]). This way, indirect effects via different pathways leading to the outcome can be examined. Model fit will be evaluated. Exploratory analyzes will examine further effect-modulating variables (e.g., treatment preferences, patient-, clinical, or treatment characteristics) as moderators (i.e., interaction effects with treatment group) or in the form of subpopulation/sensitivity analyzes (e.g., comorbidity status, treatment length, health care utilization) using the same LMMs as for the main analysis.

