### Adverse event reporting and harms {22}

Psychotherapy is generally considered safe, even though discussing personal issues can sometimes evoke strong or unpleasant emotions. The researchers do not anticipate any excess risks or negative effects for participants from the treatment or study procedures. Participants will receive high-quality outpatient psychotherapy and complete established, standardized questionnaires. There will be no special physical demands on study participation (no blood or saliva sampling, no medication or placebo administration, no invasive measurements). Potential side effects of the treatment will be systematically assessed throughout the trial by therapists using a checklist at the time of occurrence and during scheduled visits (sessions 1, 5, 10, and 15) as well as at the post-assessment and the follow-up assessment (administered by study personnel). This is done to monitor any SAEs or events that may negatively influence the course of treatment. The following SAEs will be assessed systematically: (1) death, (2) attempted suicide, (3) intentional self-injury, (4) intoxication with a psychotropic substance requiring medical treatment, (5) life-threatening event, (6) unplanned hospitalization, (7) persistent or significant disability or incapacity. In addition to SAEs, certain ESIs will also be recorded, even if they do not meet any of the above-mentioned criteria for seriousness. These include the following: suicidal ideation or plans, the development of an acute psychosis, and the breakdown of a close or important relationship. Therapists are instructed to discuss all these events and potential subsequent actions in supervision. Additionally, patient-rated potential side effects of the treatment will be assessed via standardized self-report (NEQ) at post-assessment.

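### The safety objective is framed as an absence of significant differences, which the planned difference tests cannot confirm, least of all for SAEs and other rare harms

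*Protocol article*

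**What the plan says.** The Abstract names safety among the aims and lists patient safety with the secondary outcomes. Objectives {7} gives the expectation: "no significant differences are expected in the type or frequency of serious adverse events (SAEs) and other side-effects between iSOMA+ and CBT". Trial design {8} describes a "randomized controlled superiority trial".

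The analysis is in section {20a}. For the NEQ it says "We will test group differences in the type and frequency of self-reported side effects in the NEQ with" chi-square tests, and it adds an independent t-test for severity ratings. No test is named for SAEs or events of special interest. The only sentence that could cover them is the general one, "Categorical outcomes will be analyzed by" chi-square tests, which also promises absolute and relative frequencies. The 95% confidence intervals in {20a} belong to the adjusted mean differences from the mixed model. None is stated for a safety comparison, and no margin is given.

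On timing, Outcomes {12} says "Self-rated negative treatment effects will be assessed post-treatment by the Negative Effects Questionnaire". Section {22} records the prior view: "The researchers do not anticipate any excess risks or negative effects for participants from the treatment or study procedures". The sample size in {14} is worked out for the primary endpoint only.

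**The concern.** The hypothesis is one of no difference, but the tests are built to reject no difference. When such a test fails to reject, the cause may be similar rates or too few events, and the p-value does not say which. The fewer the harms observed, the more readily the stated expectation appears to be met.

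At stake is what the trial can report on one of its named aims. For uncommon harms, a non-significant result is likely even if the blended arm has twice the rate. Set beside the wording of the objective, that result invites a statement of comparable safety that the data could not support.

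**Working it through.** **The plan's own figure.** Inputs from {14}: d = 0.40, two-sided alpha 0.05, power 80%, drop-out up to 20%. The normal approximation gives 2 × (1.960 + 0.842)² / 0.40² = 98.1, so 99 per arm. The t-test version gives 99.08, so 100 per arm and 200 in total. Allowing for drop-out, 200 / (1 − 0.20) = 250, or 125 per arm. The stated 200 and 250 are reproduced. No corresponding figure exists for safety.

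**Numbers available for safety.** SAEs are recorded by therapists during treatment and by study personnel afterwards, so up to 125 per arm can contribute. The NEQ is completed only post-treatment, so with 20% drop-out about 125 × 0.80 = 100 per arm remain.

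**Power against a doubling.** Control rates are assumptions. The test is a two-sided 5% chi-square test without continuity correction. The normal approximation is Φ[(Δ − 1.96 × SE₀) / SE₁], with Δ the risk difference, SE₀ the pooled and SE₁ the unpooled standard error. For 5% versus 10% with 125 per arm:

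- SE₀ = √(2 × 0.075 × 0.925 / 125) = 0.0333
- SE₁ = √((0.05 × 0.95 + 0.10 × 0.90) / 125) = 0.0332
- (0.05 − 1.96 × 0.0333) / 0.0332 = −0.46, so power is about 0.32

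Exact enumeration of the chi-square test gives:

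| Control vs doubled rate | Power, 125 per arm | Power, 100 per arm | n per arm for 80% |
|---|---|---|---|
| 2% vs 4% | 13% | 11% | 1141 |
| 5% vs 10% | 32% | 27% | 435 |
| 10% vs 20% | 60% | 52% | 199 |
| 15% vs 30% | 82% | 73% | 121 |
| 20% vs 40% | 94% | 88% | 82 |
| 30% vs 60% | >99% | 99% | 42 |

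(The last column uses the normal approximation.) Fisher's exact test is weaker for rare events: 24% and 19% for 5% versus 10% with 125 and 100 per arm.

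**What equal observed rates would exclude.** With 125 per arm and the same observed rate p in both arms, the upper 95% limit of the risk ratio is exp[1.96 × √(2(1 − p) / (125p))]. At p = 5% this is exp[1.96 × √(1.90 / 6.25)] = exp(1.08) = 2.95. It is 5.67 at 2%, 2.10 at 10% and 1.64 at 20%. The 95% half-width for the risk difference at 5% is 1.96 × √(2 × 0.05 × 0.95 / 125) = 5.4 percentage points. That is wider than the 5 points by which a 5% rate would rise if it doubled.

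**NEQ severity.** With 100 per arm, the t-test has about 80% power for d = 0.40, the same as the primary endpoint.

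**The case against.** The strongest reply is that the objective voices an expectation and sets no decision rule. It says that safety will be investigated and that no significant differences are expected, in line with {22}. A reader might infer that a non-significant p-value will be declared to show equal safety, but no sentence says so. That part of the reply stands: such a reading is a foreseeable use of the wording, not a written criterion.

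Three other strong readings also go too far.

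- A reader might take it that SAEs will be tested by chi-square. The protocol names that test for the NEQ. For SAEs it follows only from the general sentence on categorical outcomes, and the detail may properly sit in the SAP.
- A reader might conclude that every safety comparison is underpowered. For side effects at 15% to 20% or more in controls this is not so, and the severity comparison is adequately powered for a moderate effect.
- A reader might say that the cells will be too small for chi-square once events are split by type. Without event rates this cannot be asserted, and changing to an exact test is a routine matter.

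The plan also has real safeguards. SAE categories are prespecified, frequencies are to be reported, and an independent DSMB with a biostatistician reviews safety twice a year. These protect participants and show the raw counts. They do not settle how the final comparison between arms is interpreted. An SAP could add intervals, but the hypothesis in {7} would still be phrased in terms of significance.

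**Conclusion.** The point holds in a limited form. The safety hypothesis is stated as non-significance, the side-effect tests that the protocol does name are difference tests, and no margin is attached. A non-significant result therefore cannot confirm the hypothesis at any sample size. The practical weakness is greatest for SAEs and other rare harms. At assumed control rates of 5% or below, a doubling would be missed about two times in three or more, and at 10% about four times in ten with 125 per arm. At 15% and 20%, power against a doubling is 73% to 82% and 88% to 94%.

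All harm rates are assumptions, because the documents give none. The SAE figures further assume that the general chi-square rule would be applied. The primary efficacy result is not affected.

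**What to change.** Reword the safety sentence in Objectives {7} as estimation: describe and compare the type and frequency of SAEs and side effects between arms, without an expectation phrased as significance. In {20a} or the SAP, report event rates by arm with risk differences and 95% confidence intervals, alongside or in place of the chi-square tests. Use an interval method suited to sparse events where counts are small. State that a non-significant difference will not be interpreted as comparable safety.

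If the investigators want to claim comparable safety, they should fix before unblinding the difference that would matter, and make the claim only if the interval excludes it. Otherwise the data should be called inconclusive.

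This needs no extra patients, visits or data. The cost is a change of wording and a more modest safety claim, since for rare events the likely conclusion is that the trial cannot tell.
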